## Abstract

**Background::**

Cardiovascular diseases remain the most common causes of death in the world. Instructions for secondary prevention recommend multifaceted approach in cardiovascular diseases risk management. Center-based physical exercise training is considered as an important integral part of cardiac rehabilitation (CR). Despite all recognized benefits CR brings, active interest of patients remains low in many countries, including the Czech Republic. That is why there is a need to focus on more effective patients’ participation in CR with respect to their preferences and needs. One of possible approaches is using telemonitoring guidance based on obtaining data via technological equipment during home exercise training. The aim of this study is to compare effectiveness of both center- and home-based exercise training with focus on participants’ physical fitness and quality of life.

**Methods/design::**

This randomized control trial intends to monitor cardiorespiratory health indicators and quality of life of patients diagnosed with a coronary artery disease (CAD) at the University Hospital Brno, Czech Republic. These patients will be randomly separated into 2 groups—a regular outpatient group (ROT) and an intervention training group (ITG). Both groups undergo a 12-week rehabilitation training program. The ROT group will undergo center-based exercise trainings in the hospital and receive feedback and support directly by their coach. The ITG group will be telemonitored during exercise training in their home environment via a wrist sport tester and Internet application.

All patients will be supposed to exercise at 70% to 80% of their heart rate reserve obtained from cardiopulmonary exercise test (CPX). The primary outcome is to measure and compare physical fitness values assessed at baseline and after 12 weeks of training. Physical fitness is expressed as peak oxygen uptake assessed by the CPX test. The secondary outcomes are patients, training adherence, and their quality of life.

**Discussion::**

This trial focuses on an up-to-date topic. As there have not been any similar trials in the Czech Republic yet, we expect it to bring great benefits not only for our hospital in Brno. In the long term, this method seems to be low-cost for all participants and brings a lot of benefits for those patients, who are for many reasons unable to participate in center-based CR provided by hospitals and other health care centers. Physical exercise therapy brings good results in reducing cardiovascular risk factors and improves its global impact. Thanks to its simplicity, it is expected to increase patients’ training adherence as well.

## Background

1

Cardiovascular diseases have been, already for a long time, the most common causes of death in the world.^[1]^ These diseases are related to high blood pressure, cholesterol, diabetes, and smoking.^[2]^ The most common cardiovascular causes of death are coronary artery diseases (CAD) and cerebrovascular diseases. In 2014, the CAD caused 126 deaths per 100,000 inhabitants in the whole EU-28. The standardized CAD mortality rate in the Czech Republic in 2014 was 333.1 deaths per 100,000 inhabitants. One year later the Czech Statistical Office published its results, proving that 42% of men and 50% of women deaths were caused by CAD. On the whole, CAD caused 51% death cases from the whole number of 111,173 deaths, which is alarming 46%.^[3]^

Health care in the Czech Republic system is being financed mainly from public health insurance, some patients partially cover the costs themselves just in occasional cases. In an international comparison of health care expenses, the Czech Republic is highly above the average in Europe (42%).^[4]^

Czech health insurance companies pay most money for cardiovascular diseases treatment. In 2016 it was 25.4 billion CZK, which was 10.7% of all the health care expenses that year.^[5]^

With life expectancy still increasing (between 2006 and 2016 life expectancy grew from 73.4 to 79.7 for men and from 76.2 to 81.2 for women)^[6]^ and medical treatment improving, these expenses are expected to grow significantly in the future.^[7]^ It is necessary to deal with this fact and search for solutions how to prevent or at least significantly reduce these diseases.

One of possible ways of cardiovascular diseases prevention is a cardiac rehabilitation as a complex secondary intervention, where physical exercise training plays crucial role.

At the same time, it shows people how to develop, accept, and lead a healthy lifestyle.^[8]^

Heran et al's study discovered that CR can reduce the total mortality rate by 13% and cardiovascular mortality by 26%.^[9]^ The Czech Republic provides this preventative care only in hospitals and medical centers under a specialist's supervision.^[10]^ Despite recognized benefits, the active patients’ participation remains low.^[11]^

Main factors why patients miss the CR training seem to be technical complications. Above all, they mention commuting difficulties, time demandingness, and concrete training program timing. A social factor plays an important role too.^[12]^

Another disadvantage of CR guided by hospitals is its momentariness. Patients undergo a prescribed monitored training program and then they are discharged from the hospital without any possibility to get feedback regarding blood pressure, heart rate, or individual training care.^[13]^ That is why it is necessary to focus on the possibility of a long-term CR intervention besides the one provided by hospitals and medical centers.

One of the effective ways is to move a part of CR to patient's home environment. Meta-analysis^[14]^ of the Cochrane health database revealed insufficient differences between home- and hospital-based CR training from a short-term point of view. However, studies evaluating long-time effects referred to more significant results. For example, Smith et al's study ^[15]^ showed a decline in peak VO_2_ between 1 and 6 years follow-up in both the home- and hospital-based group, but the rate was significantly smaller in the home-based group.

Committee for Practice Guidelines of the European Society of Cardiology^[16]^ came to conclusion that CR should focus not only on risk factors modification and patients’ pharmacological adherence, but it should also provide patients with other different possibilities, such as using telemedicine.

Systematic review of earlier telemedical studies revealed a significant influence of cardiovascular risk factors, including adherence, total cholesterol, HDL cholesterol, and systolic blood pressure.^[17]^

Although the current findings highlighted benefits of telemedicine, previous researches confined themselves to technologies binding patients to concrete places. It is necessary to explore technologies supporting flexibility of training program.

Web and mobile technologies are receiving attention as an alternative approach to support changes in human behavior, clinical improvement, and better social function of patients.^[18]^ For example, providing care via short message system can help in curing many chronic diseases, such as diabetes and asthma.^[19]^ Recently, finished randomized study Telerehab III^[20]^ presented an intervention using short message system and Internet in mobile phone as an efficient, cost-effective way to provide health care. In comparison to a control center-based group of patients, who got a usual care, patients in home-based group using mobile phones pointed out that their quality of life and motivation to be physically active have significantly increased.

This study was also an important source of information about how mobile phones can be effective in modern medicine. However, it is necessary to monitor physical exercise trainings in detail to provide patient with information about required heart rate, intensity, and training duration.^[21]^ Practicability of distant monitoring has been recently proved by using smartphones, ECG sensors, and GPS device.^[22]^ The 6-week-long program decreased patients’ depression and improved walking performance and physical health related to quality of life.

Fit@Home study^[23]^ from 2017 presented positive results when using a heart rate monitor. However, it mentions great limitations, such as lack of blinding for the physician regarding patient's allocation, and some patients’ discomfort while wearing the chest strap of the heart monitor.

Nevertheless, telemedicine brings great benefits, although it needs another randomized control studies to get more statistically significant data related to this approach.

## Methods

2

Participants of CR-GPS project, as a single prospective randomized controlled trial, will be the patients of University Hospital (UH) Brno, Czech Republic, above the age of 18, diagnosed with CAD (angina pectoris, myocardial infarction, patients after coronary revascularization) in the last 6 months, with left ventricular ejection fraction >45%.

All eligible patients will be recommended by physiotherapists and research assistants from UH Brno. They must be clinically stable, able to undergo CPX, understand and write in Czech, and agree to participate in this project. Due to a random separation into 2 groups, all of them must have a mobile phone and free access to Internet connection.

Patients participating in CR-GPS will be further classified by cardiologist according to following criteria:No significant cardiovascular riskNo implanted cardioverter-defibrillator or pacemakerNo residual partial coronary artery stenosis requiring revascularizationNo orthopedic or neurological disability to exerciseNo mental disadvantage making cooperation impossibleNo serious oncological disease or treatment

During CR-GPS, some health problems might occur. If physical status of any participant changes significantly, he or she will be examined by the cardiologist who might change the medication. If this health problem becomes serious, this patient will be excluded from the trial. The obtained data of such patient will be further secured but not involved in final statistical evaluation.

According to Vysoký et al's study,^[24]^ number of participants calculation will be based on the improvement of peak VO_2_ 3.2 mL/kg/min with standard deviation 4.2 mL/kg/min. We will need 56 participants to reach 80% of statistical power with significance level set at *P* < .05. We count with 10% participant loss during the trial.^[25]^

At the beginning of the trial, all participants undergo baseline assessment on cycle ergometer (Ergoline Ergoselect 100, Bitz, Germany) and cardiologist will test their physical fitness through CPX. After that, they obtain a study package containing personal data questionnaire (sex, age, weight, diagnosis, pharmacological treatment), list of trial information, and informed consent form.

Personal information will be sent to research team from UH Brno. They will be processed and backed up according to currently valid General Data Protection Regulations (GDPR). A total of 56 patients will be separated to ITG using a telemedicine assistance and ROT group with regular center-based CR. This separation will be random, done by a computerized allocation system applying an algorithm in proportion 1:1. Investigators will not be aware of the randomized matching sequence. The patient and care providers are not blinded to the intervention.

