### Statistical analysis

3.4

Baseline characteristics assessed from the questionnaire will be summarized using descriptive statistics. A paired *t* test will be used to find out whether there are statistically significant changes between baseline and final physical fitness values and values describing health-related quality of life. Between-group differences in physical fitness values will be evaluated by analysis of variance (ANOVA). Training adherence data will be expressed as percentage. For all statistical comparisons, the significance level will be set at *P* < .05. Analyses of all metric data (ANOVA and paired *t* test) will be processed in the statistical software Statistica 12.

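### Participants with a serious health problem during the trial are dropped from the final analysis, so the groups compared are no longer those randomised and the results can be biased

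*Protocol article*

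**What the plan says.** The rule stands in section 2 (Methods) of the protocol article. It opens with the time frame, "During CR-GPS, some health problems might occur", and provides for examination by the cardiologist if a participant's condition changes significantly. It then says: "If this health problem becomes serious, this patient will be excluded from the trial". On the data it says: "The obtained data of such patient will be further secured but not involved in final statistical evaluation". The article does not define what makes a problem serious.

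The same section describes a randomised comparison, with allocation "done by a computerized allocation system applying an algorithm in proportion 1:1", and says of blinding: "The patient and care providers are not blinded to the intervention".

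Section 2.1.3 lists physical fitness as the main outcome, with quality of life and training adherence as secondary outcomes. Section 3.4 plans paired t tests for change in fitness and quality of life, ANOVA for the between-group difference in fitness, and percentages for adherence. Nothing in the article brings the removed patients back into any analysis.

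**The concern.** Randomisation makes the two groups comparable at allocation. Removing people for something that happens afterwards keeps that comparability only if the removals are unrelated to arm or unrelated to outcome. Here both conditions are doubtful.

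- **Arm.** Both groups train at the same target intensity. Under section 2.1.2 the centre group is directly supervised, with heart rate and blood pressure monitored. Under section 2.1.1 the home group has two supervised sessions, then trains at home with a weekly telephone check. The frequency of serious problems, or the chance that one is noticed, may therefore differ.
- **Outcome.** A patient who deteriorates would plausibly have a poorer peak VO2 change, a worse SF-36 and fewer completed sessions. These are all the outcomes that the article lists.

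At stake is the trial's main question, how home training compares with centre training in the patients assigned to each. The within-arm results are affected too, because the Discussion expects significant improvement in both groups, and deleting the patients who did worst makes that easier to show. With 28 patients per arm, a few removals count.

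**Working it through.** **Inputs from the article.** Planning values "3.2 mL/kg/min with standard deviation 4.2 mL/kg/min"; 56 participants, allocated 1:1, so 28 per arm; 80% power at the 5% level; 10% participant loss from any cause.

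**Inputs not in the article, therefore assumed.** The number k removed from one arm, and the mean change x that they would have had. The retained patients' mean gain is set at the planning value of 3.2 mL/kg/min.

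**1. The plan's own figure.** The article says: "We will need 56 participants to reach 80% of statistical power with significance level set at" 5%. For two means, two-sided, normal approximation:

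n per arm = 2 × (1.96 + 0.84)² × 4.2² / 3.2² = 2 × 7.85 × 17.64 / 10.24 = 27.04, rounded up to 28, or 56 in total.

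The figure reproduces. A two-sample t test gives 28.04 per arm, and 79.9% power at 28. The concern does not rest on the sample size.

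**2. Shift in one arm's mean.**

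Full-arm mean = ((28 − k) × 3.2 + k × x) / 28. The analysis reports 3.20, so overstatement = (k / 28) × (3.2 − x).

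| k removed | x | Full-arm mean | Overstatement | Share of 3.2 |
|---|---|---|---|---|
| 2 | 0 | (26 × 3.2 + 0) / 28 = 2.97 | 0.23 | 7% |
| 3 | −1 | (25 × 3.2 − 3) / 28 = 2.75 | 0.45 | 14% |
| 4 | −2 | (24 × 3.2 − 8) / 28 = 2.46 | 0.74 | 23% |

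The planned loss is 10% of 28 = 2.8 per arm from all causes, so k = 4 (14% of one arm) lies above it. A wider grid, with 1 to 3 removed and a deficit of 2.1 to 6.4 against retained patients, runs from 1/28 × 2.1 = 0.075 to 3/28 × 6.4 = 0.69 mL/kg/min (2% to 21% of 3.2).

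**3. From one arm to the comparison.** Bias in the difference = overstatement in one arm − overstatement in the other.

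- All removals in one arm: the whole shift enters the comparison, in favour of that arm.
- Three removed from each arm with x = −1: the bias is 0.45 − 0.45 = 0, but each arm still reports 3.20 instead of 2.75.

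**4. Scale.** The standard error of the difference is 4.2 × √(2/28) = 1.12, so 0.45 is about 0.4 standard errors. With no true difference, 10% removed from one arm only and a deficit of 3.2, the shift is 0.32. The standard error is 4.2 × √(1/28 + 1/25.2) = 1.15, and the two-sided rejection rate is about 5.9% instead of 5%. At a deficit of 6.4 the shift is 0.64 and the rate is about 8.6%.

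**5. Numbers.** If removals and other losses bring the arms to 25 each, power at the planning values is 75.2% (t) to 76.8% (normal). Analysing all randomised patients does not itself change the required number.

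**The case against.** The best case for the rule is that it may do little. Entry is restricted to clinically stable patients with ejection fraction above 45% and no significant cardiovascular risk, so serious problems may be few. If they are alike in both arms, the bias in the comparison cancels. A patient with a serious problem may also be unable to perform a maximal week-12 test, and a complete-case ANOVA would then lose that patient anyway.

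Much of this stands. The bias is possible, not certain, and part of any shift could come from unobtainable outcomes rather than from this sentence. But the rule also discards data that do exist: completed sessions, any SF-36, and any week-12 test that was done. Nor is this a detail left to a statistical analysis plan. The article states the exclusion outright, and a plan that analysed everyone would contradict it.

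A reader might infer three stronger things that the documents do not support.

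- **That the rule hides harm.** The data are to be kept, and nothing says that health events or exclusions go unreported. Safety reporting is commonly left to the full protocol, so its absence from an article proves nothing.
- **That seriousness is judged with knowledge of the arm.** Patients and care providers are unblinded, and a cardiologist examines the patient. The article does not say who decides that a problem is serious, or whether that person knows the allocation.
- **That the rule favours home training.** No direction follows from the documents. The illustrations place all removals in one arm by assumption.

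**Conclusion.** The concern holds in this form: the exclusion rule is wrong as written for a randomised comparison. It removes participants for an undefined event after randomisation that is plausibly related to every listed outcome and may differ by arm. The between-arm result can be biased in either direction, and within-arm gains and adherence can be overstated even when removals are balanced.

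The size cannot be determined from the documents. The range of 0.23 to 0.74 mL/kg/min is an illustration. It assumes 2 to 4 of 28 removed, changes of 0 to −2 in those patients, and a gain of 3.2 in the rest. It is a bias in the comparison only if the other arm loses nobody to the rule. Under such assumptions the shift is below one standard error of the difference, but not negligible against a planning value of 3.2.

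**What to change.** Amend both sentences. Changing only the one on data would leave the patient excluded from the trial, which contradicts an analysis of everyone. Suggested wording: *This patient stops training. All randomised patients are analysed in their allocated arm, using all data collected.* The decision to stop training is unchanged, and no definition of a serious problem is proposed here. That judgement would simply no longer decide who is analysed.

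In addition:

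- Obtain the already scheduled week-12 SF-36 from patients who have stopped, and the exercise test only where the cardiologist permits it.
- Handle missing week-12 values with a likelihood-based model or multiple imputation that includes baseline peak VO2.
- Add a sensitivity analysis for those who stopped for health reasons.
- Report the number who stopped, with reasons, by arm.

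The cost is a protocol amendment, slightly more analysis work, and some follow-up of patients who under the present text would have left the trial. The change itself calls for no additional patients.

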#### Outcomes

2.1.3

Main outcome is to compare physical fitness values measured at baseline and after 12 weeks in 2 groups of patients (ROT and ITG). Secondary outcomes are health related quality of life and training adherence. Health-related quality of life is measured at baseline and after 12 weeks. Training adherence is assessed in both groups during the 12 weeks of exercise period. A summary of the trial design is provided in flowchart (Fig. 1).

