## Discussion

4

Despite the fact that CR brings great benefits as a prevention of cardiovascular diseases,^[26,27]^ the regular outpatient training provided by health insurances is insufficient and physical fitness of patients usually gets worse after being discharged from the hospital.^[28]^ There are a lot of reasons why these patients refuse to train on their own. Besides the financial point of view (high expenses on individual coach), there are also problems in motivation, technical, and social issues.^[29]^ The average age of patients diagnosed with CAD is 60.4 ± 10.9 years.^[24]^ These people often suffer from depression of low mood coming from their disease and are afraid to manage their physical exercises themselves.^[13]^

Fast developing technology allows us to search for new possibilities. What we need to do is to find out how to use them in modern medicine. It is the telemedicine which has already been practiced and explored in many countries. For the Czech Republic, this way of remotely controlled patient is still unexplored and unique.

Already published foreign studies show how useful, low-cost, and successful telemedicine could be,^[30,31]^ some of them talk about even better results reached by telemedicine than center-based trainings.^[32]^ To distinguish from previous studies, we decided to try a new, in our country available tool—a wrist sport tester. Data transport from patients to physiotherapist is provided via Internet connection.

The aim of this study is to monitor 2 groups of patients (ROT and ITG groups) who will undergo a 12-week training. The ROT group will be monitored under the direct supervision by a physiotherapist in a hospital; the ITG will be monitored and checked via wrist sport tester during their home-based exercise trainings. What we focus on in our study is to compare the improvement of their quality of life and physical fitness. We expect that the improvement of both variables after 12 weeks of training will be statistically significant in both ROT and ITG groups.

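### The 56 patients give 80% power only if the two training arms differ by 3.2 mL/kg/min, a between-arm difference that the protocol neither states nor justifies

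*Protocol article*

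**What the plan says.** The sample size paragraph (Protocol article, Methods) takes its inputs from one cited study: the "number of participants calculation will be based on the improvement of peak VO_2_ 3.2 mL/kg/min with standard deviation 4.2 mL/kg/min". It continues: "We will need 56 participants to reach 80% of statistical power with significance level set at" P < .05, and allows for 10% loss. The same 56 patients are then randomised, "done by a computerized allocation system applying an algorithm in proportion 1:1", so 28 go to each arm.

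The comparison of interest is between the arms. Section 2.1.3 says: "Main outcome is to compare physical fitness values measured at baseline and after 12 weeks in 2 groups of patients (ROT and ITG"). Section 3.4 assigns ANOVA to the between-group difference in fitness and a paired t test to the change from baseline.

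Three other places bear on what difference to expect:

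- Sections 2.1.1 and 2.1.2 prescribe the same heart rate band, aerobic duration, weekly frequency and 12-week length in both arms.
- The Background reports that a meta-analysis "revealed insufficient differences between home- and hospital-based CR training from a short-term point of view".
- The Discussion states: "We expect that the improvement of both variables after 12 weeks of training will be statistically significant in both ROT and ITG groups".

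No section gives an expected difference between the arms, or a non-inferiority or equivalence margin.

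**The concern.** The word used for 3.2 suggests what training adds to peak VO2 from start to finish, yet the sample size follows only if 3.2 is what one arm achieves over and above the other. These are different quantities. When both arms train to the same prescription, the difference between them would ordinarily be only a part of the gain that each makes. If, for illustration, the centre-based arm gained 3.2, an arm difference of 3.2 would require the home-based arm to gain either 0 or 6.4.

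At stake is how the main result will be read. With 80% power on record and no margin stated, a non-significant ANOVA could be taken as good evidence that home training matches centre training. If the true power for a moderate difference is far lower, that inference fails.

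**Working it through.** **Inputs.** Effect 3.2, SD 4.2, power 80%, total 56 and loss 10% (Methods). Significance level 0.05 (Methods and section 3.4); its sidedness is not stated, so two-sided is taken first and one-sided is also tried. Allocation 1:1 (Methods). Standardised effect d = 3.2/4.2 = 0.762.

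**Step 1: reproduce 56.** Two-sample comparison, two-sided:

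n per arm = 2 × SD² × (1.960 + 0.842)² / Δ² = 2 × 17.64 × 7.849 / 10.24 = 27.04, rounded up to 28, so 56 in total.

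The t-test version needs 28.04 per arm, and 28 per arm gives 79.9% power. The stated figure is reproduced.

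**Step 2: try the alternatives.**

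| Calculation with 3.2 and 4.2 | Patients needed |
|---|---|
| Two-sample, two-sided | 56 |
| Two-sample, two-sided, inflated for 10% loss: 56/0.9 | 63 |
| Two-sample, one-sided | 44 (normal), 46 (t) |
| Two-sample, one-sided, inflated for 10% loss | 49 to 52 |
| Before-after (paired), two-sided | 14 (normal), 16 (t) |
| Before-after, 16 in each arm | 32 |

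Only the first row gives 56. So 3.2 entered as a between-arm difference, and the 10% loss was not added.

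**Step 3: completers.** 56 × 0.9 = 50.4, or about 25 per arm.

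**Step 4: power for the arm difference.** Two-sample t test, two-sided 5%, noncentrality Δ / (SD × √(2/n)). The smaller differences are assumptions, since the protocol gives none; 1.6 is half of 3.2. The SD is not labelled, so a smaller SD of change, 2.5, is assumed alongside 4.2 to show the range.

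| True arm difference (mL/kg/min) | SD 4.2, 28 per arm | SD 4.2, 25 per arm | SD 2.5 (assumed), 25 per arm |
|---|---|---|---|
| 3.2 | 80% | 75% | 99% |
| 2.0 | 42% | 38% | 79% |
| 1.6 | 29% | 26% | 60% |
| 1.0 | 14% | 13% | 28% |

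**Step 5: precision.** The 95% CI half-width for the arm difference is t × SD × √(2/n).

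- 28 per arm, SD 4.2: 2.005 × 4.2 × √(2/28) = 2.25.
- 25 per arm, SD 4.2: 2.011 × 4.2 × √(2/25) = 2.39, which is 2.39/3.2 = 75% of the quoted improvement.
- 25 per arm, SD 2.5: 2.011 × 2.5 × √(2/25) = 1.42.

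**Step 6: the before-after test.** If 4.2 is the SD of change, a paired t test for a gain of 3.2 has 97% power with 28 patients in an arm and about 95% with 25. Success in both arms has probability of about 0.973² = 95% and 0.955² = 91% respectively.

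**The case against.** **The meaning of 3.2 is inferred.** The Methods section does not say whether it is a within-group gain or a difference between groups, and the cited study is not at hand. This stands: the within-group reading is probable, not proven. It rests on the word used and on the Discussion using the same word for change within each arm. If the figure were a contrast of training with no training, it would fit two training arms no better.

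**The SD is not labelled.** This also stands. With an assumed SD of change of 2.5, power at 25 per arm is 79% for 2.0 and over 80% for 3.2. Power at smaller differences is therefore conditional. It remains true that the protocol offers no reason for an arm difference of 3.2.

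**The trial is large enough for the one expectation it spells out.** The Discussion predicts significant improvement in both arms, for which 28 per arm is ample if 4.2 is the SD of change. That is fair, but the main outcome is a comparison of the two groups, and the 80% reproduces only for that comparison.

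**The Background is not the whole picture.** The Discussion adds that some studies found telemedicine better than centre-based training. It gives no size for that advantage, so it does not supply 3.2.

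**Stronger readings that a reader might infer.** One is that the ANOVA will be non-significant whatever the truth. The figures above do not support that: a difference of 3.2 would be found about three times in four at 25 per arm with SD 4.2. Another is that the trial must be enlarged. The documents give no target difference or margin from which a larger number could be derived. A third is that one arm must gain nothing or double, which holds only if the other gains exactly 3.2.

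**Conclusion.** The point holds as a misdescribed power statement, not as an arithmetic slip. The calculation behind 56 is a valid two-sample calculation, but its effect size is a between-arm difference of 3.2 mL/kg/min that the protocol neither states nor supports, for arms that share the same prescribed intensity, duration and frequency and are both expected to improve. On the protocol's own SD and its own 10% loss, power is about 75% at 3.2 and falls to between 13% and 38% for differences of 1.0 to 2.0.

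That 56 requires an arm difference of 3.2, and that no such difference is justified, does not depend on the cited study. Two things do: that 3.2 is a before-after gain, and that 4.2 is the SD of change. If the SD of change were 2.5, the range for 1.0 to 2.0 would be 28% to 79%.

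**What to change.** Leave the sample size at 56 and rewrite the paragraph:

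1. Check the cited study and state what 3.2 and 4.2 are: a within-group gain with an SD of change, or something else.
2. Remove the unqualified 80% claim for the primary comparison.
3. Report power and precision for the arm difference at about 25 completers per arm. If 4.2 is confirmed as the SD of change: about 75% at 3.2, 38% at 2.0, 26% at 1.6 and 13% at 1.0, with a 95% CI half-width of about 2.4 mL/kg/min. If the source gives a different SD of change, recompute by the formulas above.
4. If 3.2 and 4.2 prove to be a gain and its SD, add that within-arm power is about 95% per arm at 25 completers (97% at 28).
5. Present the trial as estimating the arm difference with that precision, and say that a non-significant ANOVA will not be read as showing that the arms are equally effective.

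The cost is one rewritten paragraph and a less favourable power statement. No extra patients and no change to the training are needed.

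### The 56 patients said to be needed for 80% power are also the 56 to be randomised, so the expected 10% loss leaves about 50 and roughly 75% to 77% power

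*Protocol article*

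**What the plan says.** All the relevant statements are in section 2 (Methods) of the protocol article.

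- The basis of the calculation: "number of participants calculation will be based on the improvement of peak VO_2_ 3.2 mL/kg/min with standard deviation 4.2 mL/kg/min".
- The requirement: "We will need 56 participants to reach 80% of statistical power with significance level set at" P < .05.
- Directly after it, the loss: "We count with 10% participant loss during the trial".
- The number randomised: "A total of 56 patients will be separated to ITG using a telemedicine assistance and ROT group with regular center-based CR". Allocation is "done by a computerized allocation system applying an algorithm in proportion 1:1".
- On patients excluded because a health problem becomes serious: "The obtained data of such patient will be further secured but not involved in final statistical evaluation".

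Section 3.4 (Statistical analysis) compares the groups on physical fitness by ANOVA and uses paired t tests for change from baseline. The article gives no recruitment target larger than 56.

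**The concern.** The same number serves two purposes. It is the count needed to reach 80% power, and it is the count randomised, although a 10% loss is announced between the two. Both uses can be right only if the requirement already contains an allowance for loss, and the stated inputs allow that to be checked.

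What is at stake is the power for the primary outcome, the comparison of peak VO2 between the two groups. Section 2.1.3 (Outcomes) measures fitness at baseline and at 12 weeks, so the article shows no intermediate value that could stand in for a missing final test. If the allowance was never applied, the trial carries a higher risk of missing the stated difference than the 20% that its text implies.

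**Working it through.** **Inputs.** Difference 3.2 and SD 4.2 mL/kg/min, power 80%, loss 10%, 56 randomised 1:1 (all section 2); significance level .05 (sections 2 and 3.4). Sidedness is not stated. Two-sided is assumed, because it reproduces the plan's number and one-sided does not. With two groups, a one-way ANOVA is the two-sample t test.

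**Step 1: reproduce 56.** Normal formula, per arm:

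n = 2 × [SD × (z₀.₉₇₅ + z₀.₈₀) / difference]² = 2 × [4.2 × (1.960 + 0.842) / 3.2]² = 27.04, rounded up to 28 per arm, 56 in total.

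Power at 28 per arm:
- Normal approximation: Φ(3.2 / (4.2 × √(2/28)) − 1.960) = Φ(2.851 − 1.960) = 81.3%.
- Noncentral t, 54 degrees of freedom: 79.9%. A strict t-test calculation would need 29 per arm.

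So 56 is reproduced with no allowance for loss.

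**Step 2: other readings of the inputs.**

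| Reading | Requirement before loss |
|---|---|
| Two-sided, two arms, normal | 28 per arm, 56 total |
| One-sided, two arms, normal | 22 per arm, 44 total (49 after dividing by 0.9) |
| One-sided, two arms, t test | 23 per arm, 46 total |
| Paired t test, change within one group | about 16 patients |

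Only the first gives 56, and it does so before inflation.

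**Step 3: apply the stated loss.** 56 × 0.90 = 50.4, so about 50 evaluable, 25 per arm.
- Normal: Φ(3.2 / (4.2 × √(2/25)) − 1.960) = Φ(2.694 − 1.960) = 76.8%.
- Noncentral t, 48 degrees of freedom: 75.2%. With 51 evaluable (25 and 26) it is 76.0%.

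Like for like, power falls from 81.3% to 76.8% (normal) or from 79.9% to 75.2% (t test).

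**Step 4: the alternative that 56 is already inflated.** About 50 evaluable patients would then have to give 80% power. Step 3 shows that they do not.

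**Step 5: what would close the gap.**
- To keep 56 evaluable: 56 / 0.90 = 62.2, so 63 randomised, or 64 for equal arms. With 62, 62 × 0.9 = 55.8 falls just short.
- To keep 56 randomised: the difference detectable with 80% power at 25 per arm is 3.40 mL/kg/min by t test.

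**The case against.** **The 3.2 may not be a between-arm difference.** Section 2 calls it an improvement, section 3.4 plans paired t tests, and section 4 (Discussion) expects significant improvement in both groups. If 3.2 and 4.2 describe change within a group, about 16 patients per group suffice and 25 per group give about 95% power, so a 10% loss would do that test no harm. This stands as a caveat: the power figures depend on the between-arm reading, which is an inference. It is the better supported one, because it alone reproduces 56 and section 2.1.3 makes the group comparison the main outcome. It does not reconcile the text either, since the within-group reading leaves 56 unexplained.

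**The shortfall is small.** This also stands. It is about 5 points, and quoting 75% alone gives the lower end of a range that runs to 77% with the method.

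Three stronger readings are tempting, and the article does not support them.

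- A reader might infer that the whole 10% drops out of the analysis under the exclusion rule. That rule covers only patients excluded for serious health problems. The article does not say how other losses are handled, or that the 10% consists of such exclusions.
- A reader might infer that adjusting for baseline would restore most of the lost power. That needs a correlation the article does not give. If 4.2 is an unadjusted SD, then at 25 per arm, with the SD multiplied by √(1 − r²), t-test power is about 76% at r = 0.1, 79% at r = 0.3 and 86% at r = 0.5. It could recover almost nothing or more than everything. The article also does not say whether 4.2 is an SD of change or of level.
- A reader might infer that the comparison itself is compromised. A smaller evaluable number lowers power; it does not affect the validity of the test.

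**Conclusion.** The point holds at moderate severity. The article's requirement, expected loss and number randomised cannot all be true together. On its own inputs the design delivers about 75% to 77% power, not 80%, and by t test the risk of missing a difference of 3.2 rises from about 20% to about 25%. This does not depend on an unseen analysis plan, because every figure in the conflict is printed in the article.

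It rests on four assumptions: 3.2 (SD 4.2) is a between-arm difference, the test is two-sided at 5%, the loss is 10% and spread about equally over the arms, and lost patients contribute no 12-week value.

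**What to change.** Keep 56 and restate the power in section 2, for example:

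> *56 patients will be randomised; allowing for 10% loss, about 50 evaluable patients give about 75% power (two-sided 5%, t test) for a between-arm difference of 3.2 mL/kg/min (SD 4.2), or 80% power for a difference of about 3.4.*

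Before this wording is used, the sponsor should confirm that 3.2 is meant as the between-arm difference. If it is not, the basis of the 56 has to be explained instead. The restatement should not promise any gain from baseline adjustment.

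The cost is one sentence and a stated power about 5 points lower. If the sponsor prefers to hold 56 evaluable patients, the alternative is to randomise 63, or 64 for equal arms: 7 or 8 more than planned.
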